### 2.10. Initial Observational Feasibility Phase

Prior to the randomized trial, an initial observational feasibility phase will be conducted, including approximately 60 consecutive patients who undergo clinically indicated CCTA followed by subsequent PCI procedures in the GRN Hospital Weinheim. In this phase, anonymized CCTA datasets will be analyzed at the University Hospital Zurich to evaluate image quality, completeness of reconstructions, and clinical applicability of the CCTA-derived procedural planning parameters. The purpose of this phase is to assess workflow integration, verify technical feasibility and post-processing, and refine the standardized reporting template for use in the randomized study. Data obtained during this phase will not be used for hypothesis testing but will serve to validate study logistics and optimize the design of the subsequent randomized trial. In particular, the use of intravascular ultrasound (IVUS) is encouraged during this pilot study phase to verify CCTA findings using intravascular imaging. Figure 2 presents the basic information provided by the Cardiac Imaging Department of the University Hospital of Zurich for each patient during the pilot phase. This information includes maximum MIP images and MIP-based representations of the coronary anatomy; assessment of coronary ostial takeoff (clock-face orientation and height from the aortic annulus); curved and straight MPR images; orthogonal cross-sectional views of the coronary arteries; recommended optimal angiographic projection angles; and procedural suggestions for PCI planning.

### 2.11. Statistical Analysis

Descriptive statistics will be used to characterize the patient population, procedural details, and outcomes. Categorical variables will be reported as counts and percentages and compared using the chi-square or Fisher’s exact test. Continuous variables will be assessed for normality using the Shapiro–Wilk test. Variables that are normally distributed will be presented as mean ± standard deviation and compared using *t*-tests, while non-normally distributed variables will be presented as median (interquartile range) and compared using Mann–Whitney U tests. To assess the impact of CT planning on procedural outcomes, univariate and multivariable logistic regression models will be applied. Variables with a *p*-value < 0.10 in univariate analysis will be included in the multivariable models using a backward stepwise approach. Odds ratios (OR) with 95% confidence intervals (CI) will be reported. The primary analysis will be performed according to the intention-to-treat principle.

Procedural metrics (e.g., contrast volume, fluoroscopy time, radiation dose, procedure duration) will additionally be assessed using linear regression models. Receiver operating characteristic (ROC) curve analyses will be performed to evaluate the diagnostic performance of specific CT features (e.g., ostial angle, lesion length, plaque morphology) for predicting procedural complications or strategy changes. The area under the curve (AUC) with 95% CI will be calculated. Interobserver and intraobserver variability for CCTA-derived measurements (e.g., ostial height, takeoff angle, lesion length) will be assessed using intraclass correlation coefficients (ICC) for continuous variables and Cohen’s κ for categorical variables.

The planned sample size of *n* = 200 patients (100 per arm) who will ultimately undergo PCI is based on prior published data on CT-guided PCI and institutional experience [3]. Since the components of the primary composite procedural optimization score have not previously been combined in a randomized trial, exact event rates are unknown. For sample size calculation, we assumed an event rate of approximately **5****0%** and a **20% absolute reduction** in the CCTA-guided arm, based on extrapolation from observational CT-guided PCI studies and institutional experience. While these assumptions may not be completely fulfilled in our real-world study setting, they provide a reasonable framework to ensure >80% statistical power to detect differences in the primary composite endpoint with a two-sided α level of 0.05 and type II error (β) of 0.20. Randomization will be performed using sequentially numbered, opaque, sealed envelopes opened immediately before PCI. Strict handling procedures are in place, and all envelope use is logged to maintain allocation concealment and integrity. Exploratory post hoc analyses will assess whether the effect of CCTA-guided planning differs according to age, sex, lesion complexity, calcification severity, bifurcation involvement, and ostial lesion location. Missing data will be handled using multiple imputation if >5% of values are missing for key variables; otherwise, complete case analysis will be performed. All statistical tests will be two-sided, with *p*-values < 0.05 considered statistically significant. Analyses will be performed using R (v4.3.1) and SPSS (v29).

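### The adjusted odds ratio for CT planning comes from p<0.10 screening and backward selection that do not exempt the randomised arm, so it can vanish and is exaggerated when it survives.

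*Protocol article*

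**What the plan says.** Everything relevant is in section 2.11 of the protocol article.

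- Purpose and model: "To assess the impact of CT planning on procedural outcomes, univariate and multivariable logistic regression models will be applied".
- Selection rule, in the next sentence: variables below a p-value of 0.10 "in univariate analysis will be included in the multivariable models using a backward stepwise approach".
- Effect measure: "Odds ratios (OR) with 95% confidence intervals (CI) will be reported".
- Population: "The primary analysis will be performed according to the intention-to-treat principle". This sentence names no model.
- Unselected comparison, earlier in the same section: "Categorical variables will be reported as counts and percentages and compared using the chi-square or Fisher’s exact test".
- Size and assumptions: "The planned sample size of *n* = 200 patients (100 per arm) who will ultimately undergo PCI"; "we assumed an event rate of approximately 50% and a 20% absolute reduction in the CCTA-guided arm"; "with a two-sided α level of 0.05 and type II error (β) of 0.20". The section adds that these assumptions may not be fully met.

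No sentence forces the randomised arm into the multivariable model, and none says which variables are candidates. Section 2.8 lists what is collected. It mixes baseline items (age, risk factors, Agatston score) with procedural ones (intracoronary imaging, number of stents, lesion modification, contrast volume, radiation).

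**The concern.** In a randomised comparison the arm belongs in the model whatever its p-value, because its coefficient is the quantity being estimated. Under the rule as written, the arm must first reach p < 0.10 on its own and then survive elimination. This has two consequences.

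- In some trials there is no adjusted treatment effect to report.
- In the rest, the reported value has been selected for being large, so on average it lies too far from 1. Its nominal 95% interval ignores the selection.

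The text also leaves room for procedural variables to pass the screen. Intravascular imaging, contrast volume and radiation dose feed the primary composite (section 2.9), so they would be expected to be associated with it. Adjusting for them would condition on part of the outcome, or on the path from CT planning to it.

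**Working it through.** **1. The plan's own figure.** Inputs from section 2.11: 100 per arm, 50% vs 30%, two-sided α 0.05. With the pooled rate (0.50 + 0.30)/2 = 0.40:

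z = [0.20·√100 − 1.96·√(2·0.4·0.6)] / √(0.5·0.5 + 0.3·0.7) = (2.000 − 1.358)/0.678 = 0.947, so power = Φ(0.947) = 82.8%.

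This agrees with the stated >80%. It is the power of an unadjusted comparison of two proportions, and 80% power needs 93 per arm. Nothing below changes the sample size.

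**2. The screen alone.** This needs no assumption about covariates. For control rate 0.5 and treated rate q:

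- β = ln[q/(1−q)], since the control log odds are 0
- SE = √[1/50 + 1/50 + 1/(100q) + 1/(100(1−q))]
- m = |β|/SE
- P(arm passes p < 0.10) ≈ Φ(m − 1.645)
- mean exaggeration of the log odds ratio when it passes ≈ 1 + φ(m − 1.645)/[m·Φ(m − 1.645)]

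| True rates | True OR | SE | m | Passes (formula) | Exaggeration (formula) | Dropped (simulated) | Exaggeration (simulated) | OR when kept (simulated) |
|---|---|---|---|---|---|---|---|---|
| 50% vs 30% | 0.43 | 0.296 | 2.86 | 89% | 1.08 | 10.5% | 1.08 | 0.40 |
| 50% vs 35% | 0.54 | 0.290 | 2.14 | 69% | 1.24 | 30% | 1.25 | 0.46 |
| 50% vs 40% | 0.67 | 0.286 | 1.42 | 41% | 1.67 | 58% | 1.67 | 0.51 |

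The simulated columns come from 400,000 pairs of binomial counts per row and match the formula closely.

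**3. The full rule against a fixed model.** There were 2,000 simulated trials per scenario. Assumptions not in the article: stay level 0.10, and ten standard-normal covariates, four prognostic (log odds 0.6, 0.5, 0.4, 0.3) and six null. Intercept and treatment effect were calibrated so that the overall event rates equal those shown. The true adjusted ORs (0.37, 0.48, 0.62) lie further from 1 than the crude ones because the odds ratio is not collapsible. Exaggeration is measured against these adjusted values. The fixed model holds the arm and the four prognostic covariates.

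| True reduction | Arm dropped | Exaggeration, stepwise | Exaggeration, fixed | Significant, stepwise | Significant, fixed |
|---|---|---|---|---|---|
| 20 points | 12% | 1.09 | 1.03 | 84.8% | 87.7% |
| 15 points | 34% | 1.27 | 1.05 | 61.2% | 65.9% |
| 10 points | 63% | 1.69 | 1.03 | 29.8% | 33.1% |
| none | 94% | – | – | 4.0% | 4.7% |

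**4. Sensitivity to the covariates.** With 26 covariates (four prognostic at log-OR 0.4) and the same calibration, 1,500 trials per scenario keep the arm in 88%, 66% and 37%. The OR when kept is 0.35, 0.41 and 0.45, against true adjusted values of 0.38, 0.49 and 0.63. The fixed model gives 0.37, 0.48 and 0.62. Power at 20 points is 83.9% vs 87.2%. The pattern does not depend on the choice of ten covariates.

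**5. Interval coverage given that the arm passes the screen (set-up of step 2).** Coverage is 97% at a 20-point reduction, 93% at 10 points, 80% at 5 points and 46% with no effect. The interval misleads when the true effect is small or absent, not at the design effect.

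**The case against.** The best defence is that an unselected estimate exists. The univariate odds ratio for the arm is computed before any screening, and categorical outcomes are also compared by chi-square or Fisher's exact test. The stated power matches that unadjusted comparison. This stands, and it confines the point to the adjusted odds ratio. A reader might infer that the stepwise model is the primary analysis or the only estimate of the treatment effect. No sentence says so.

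The authors may also have meant the rule for covariates only, with the arm always present. That is plausible, but the selection sentence follows directly on the one about the impact of CT planning and makes no exception.

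Three other strong readings are tempting and not supported:

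- *The rule produces false positives.* It does not. With no effect, 4.0% of trials are significant under the full rule and 4.7% under the fixed model.
- *The arm is lost in nearly a quarter of trials at the design effect.* A simulation with a conditional OR of 0.43 and four covariates of log-OR 0.4 keeps the arm in 77%. That set-up implies a treated rate of 32.2%, not the article's 30%. Calibrated to 50% vs 30%, the loss is about 12%.
- *Procedural variables will be adjusted for.* Section 2.8 is a data-collection list, not a list of model candidates. The text leaves such adjustment open but does not plan it.

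A full analysis plan could hold the covariate list, and its absence from an article is no fault. The selection rule, however, is stated here and is not a missing detail.

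**Conclusion.** The concern holds for the adjusted odds ratio and its confidence interval, and for nothing wider. At the design effect the harm is modest: the arm is dropped in about 11–12% of trials, the log odds ratio is exaggerated by about 8–9% when kept (about 3% with a fixed model), and power is about 84–85% against 87–88%. It becomes serious if the true reduction is smaller, which section 2.11 itself allows for. At 15 and 10 points the arm is dropped in about 30–34% and 58–63% of trials, and the log odds ratio is exaggerated by about 25% and 67%.

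The screen-only figures rest on the article's control rate and arm size and a Wald test; the 15- and 10-point reductions are scenarios. The full-rule figures also rest on assumed covariate numbers and effects and on the 0.10 stay level. The rule should be changed, but it does not invalidate the unadjusted comparison or the sample size.

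**What to change.** In section 2.11, and in the analysis plan if there is one, replace the selection rule for every model that estimates the treatment effect:

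- always retain the randomised arm;
- adjust only for a short prespecified list of variables measured before randomisation in both arms, for example age and Agatston score from section 2.8;
- use no univariate screening, no stepwise removal, and no procedural or other post-randomisation covariates.

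Keep stepwise selection, if wanted, for exploratory prediction of complications or strategy changes, and label it so.

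Bifurcation anatomy needs care as a covariate. It is not in the CCTA list of section 2.8, and the structured report that describes it goes only to the CCTA-guided arm in the randomised phase (section 2.7). It qualifies only if read before allocation in both arms.

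The cost is a change of wording, made before outcome data are examined by arm. With covariates such as age and Agatston score it needs no new data and no more patients.

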## Abstract

**Background:** Coronary computed tomography angiography (CCTA) is a well-established key diagnostic modality for ruling out obstructive coronary artery disease (CAD) in patients with suspected chronic coronary syndromes (CCSs) and low to intermediate pre-test probability. The widespread availability of preprocedural CCTA data in CCS patients undergoing percutaneous coronary intervention (PCI), however, creates a new opportunity for image-guided procedural planning. **Objective:** The PRECISION-CT study (Prospective Evaluation of Coronary CTA Integration for Strategy Improvement and Optimization of Non-Emergent PCI) aims to evaluate the impact of CCTA-guided PCI on patient safety and clinical outcomes. **Methods:** PRECISION-CT is a prospective, two-center, randomized controlled trial, enrolling patients with CCS scheduled for elective PCI due to obstructive CAD by CCTA. Patients are randomized 1:1 to either CCTA-guided PCI or standard angiography-guided PCI. In patients randomized to CCTA-guided PCI, advanced post-processing of CCTA datasets provides specific procedural planning recommendations based on the detailed assessment of coronary artery takeoff, lesion location and plaque characteristics. In addition, real-time integration of the advanced CCTA post-processing is available in the catheterization laboratory during the PCI procedure. Patients randomized to angiography-guided PCI are treated according to routine clinical practice. **Results**: The primary endpoint is a composite procedural safety and efficacy score including: (i) need for intravascular imaging, (ii) procedural complications, (iii) post-procedural high-sensitivity troponin T elevation, (iv) contrast media, (v) radiation exposure, and (vi) length of hospital stay. Secondary endpoints include major cardiac adverse events such as cardiac death, non-fatal myocardial infarction, target-lesion reintervention and probable or definitive stent thrombosis during 1 year of follow-up. **Conclusions:** The PRECISION-CT study will provide pragmatic evidence on the ability of CT-guided PCI in patients with CCS to optimize procedural outcomes. These findings may help inform the broader adoption of image-guided precision revascularization strategies in interventional cardiology.

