
### 2.9. Study Endpoints

Primary composite endpoint (score 0–6):

The primary composite endpoint was designed to capture procedural efficiency and safety rather than long-term clinical outcomes. Individual components were selected to reflect aspects of PCI that may be directly influenced by improved preprocedural anatomical understanding and planning, including resource utilization, procedural complexity, and periprocedural myocardial injury. The composite score is intended as a pragmatic measure of procedural optimization rather than a surrogate for clinical outcome.

Need for intravascular imaging (IVUS).Occurrence of major procedural complications (perforation, severe dissection, stent malapposition, or under-expansion requiring post-dilatation, main/side branch occlusion).Post-procedural high-sensitivity troponin T elevation >5-fold compared to baseline at 24 h.Contrast volume > 200 mL as established in prior interventional studies.Radiation dose > predefined threshold (estimated effective dose of >16.1 mSv) according to institutional and published reference levels for PCI procedures [14].

Hospital stay > 2 days. Secondary endpoints (exploratory):

In-hospital MACE and complications or the need for repeated cardiac catheterization with or without reintervention during the index hospitalization or within 30 days after the procedure.

Long-term major adverse cardiac events (MACE): cardiac death, probable or definitive stent thrombosis, non-fatal myocardial infarction, or target-lesion revascularization at 12 and 24 months.

Guiding catheter changes or unplanned use of lesion preparation techniques.

Procedural efficiency metrics (procedure duration, fluoroscopy time, material consumption, and cost-effectiveness).

Patient-reported outcomes: quality of life using the SAQ-7 questionnaire.

Clinical events and complications are defined according to established consensus criteria, including Academic Research Consortium (ARC) definitions for stent thrombosis and target-lesion failure and Society for Cardiovascular Angiography and Interventions (SCAI) criteria for procedural complications. Imaging-derived findings are reported separately and are not classified as clinical events unless they meet these standardized definitions.

Figure 1 summarizes the methodological aspects and flowchart of the trial.

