Adding to the current landscape of CCTA-guided PCI in clinical practice, our study will provide pragmatic data on the correlation between preprocedural CCTA findings and actual procedural conduct and outcomes. This includes evaluating the concordance between CCTA-derived lesion assessment and angiographic complexity [21,25], the utility of CCTA in patients with prior CABG or CTO [16], and the procedural consequences of specific CT-based findings such as calcification, lesion length, and bifurcation involvement. Future directions will include the development of integrated risk models that combine CCTA and echocardiographic data of cardiac magnetic resonance metrics to guide revascularization strategies, as well as the potential use of AI-based CCTA analysis and photon-counting CT to further improve image resolution, predictive accuracy, and operator independence [26]. Ultimately, our findings will help bridge the gap between CCTA-derived anatomical assessment and real-world interventional decision-making, providing a foundation for broader implementation of structured, image-guided PCI planning in routine clinical practice.

Several limitations should be acknowledged. First, operators cannot be blinded to group allocation, introducing potential performance bias. Second, this study is powered for procedural and efficiency endpoints rather than hard clinical outcomes, which will be assessed on an exploratory basis. Third, the control group reflects contemporary CCTA-informed practice rather than the absence of CCTA, which may attenuate observed differences but which enhances real-world applicability. Finally, results from two centers with advanced imaging expertise may not be directly generalizable to all clinical settings.

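### The primary endpoint is a 0–6 score, but the sample size and the >80% power rest on a yes/no event that no section defines

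*Protocol article*

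**What the plan says.** Section 2.9 introduces the primary endpoint as "Primary composite endpoint (score 0–6" and lists six components. Contrast volume, radiation dose, troponin rise and hospital stay carry their own thresholds; the total carries none. The Abstract agrees: "The primary endpoint is a composite procedural safety and efficacy score including" the same six items. Section 2.11 also calls it a score.

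The sample-size paragraph of Section 2.11 then changes scale. It reads "For sample size calculation, we assumed an event rate of approximately" 50%, with a "20% absolute reduction in the CCTA-guided arm", a "two-sided α level of 0.05 and type II error (β) of 0.20", and 200 patients (100 per arm). It concludes that "they provide a reasonable framework to ensure >80% statistical power to detect differences in the primary composite endpoint".

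On analysis, Section 2.11 assigns tests by type of variable: chi-square or Fisher for categories, and t-test or Mann–Whitney for continuous variables. It adds: "To assess the impact of CT planning on procedural outcomes, univariate and multivariable logistic regression models will be applied". None of these is tied to the primary score. The only sentence about the primary analysis says that it follows intention to treat.

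**The concern.** A 0–6 score has no event rate until someone says which values are events. Section 2.9 gives the score without a cut-point and Section 2.11 gives the event rate without a cut-point, so the two sections describe different primary variables.

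Two things are at stake. First, the power statement is made for the primary composite endpoint but was derived for a variable the document never defines, so a reader cannot tell whether it applies. Second, at least four primary results can be read out of the text: a score of at least 1, at least 2, at least 3, or a comparison of the whole score. They have different power and can disagree. If the choice is still open when data are available, the nominal 5% no longer describes the risk of a false-positive trial. Operators are not blinded, and components such as intravascular imaging and length of stay depend partly on staff decisions, so it matters that the definition is fixed beforehand.

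**Working it through.** **Inputs from the protocol article.** Score range 0–6 and six components (Section 2.9); event rate 50%, absolute reduction 20 points (so 30%), two-sided α 0.05, β 0.20, 100 per arm (Section 2.11). The article gives no component rates, score distribution, standard deviation or expected score difference. Everything from step 2 on therefore uses labelled assumptions.

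**Step 1: reproduce the stated power.** For two proportions with p̄ = 0.40 and n = 100 per arm:

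power = Φ{[Δ − 1.96·√(2p̄(1−p̄)/n)] / √([p₁(1−p₁)+p₂(1−p₂)]/n)}

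- 1.96·√(0.48/100) = 0.1358
- √((0.25+0.21)/100) = 0.0678
- (0.20 − 0.1358)/0.0678 = 0.947, and Φ(0.947) = 82.8%

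Exact enumeration of the uncorrected chi-square test gives 83.2%. For 80% power, n = [1.96·√0.48 + 0.8416·√0.46]²/0.20² = 93 per arm. The stated >80% is therefore correct as a test of two proportions.

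**Step 2: same data, different reading.** Assume six equal, independent components, and let the planned 50% versus 30% refer to any component. The rate per component is 1 − 0.5^(1/6) = 10.9% in the control arm and 1 − 0.7^(1/6) = 5.8% in the CCTA-guided arm. Binomial tails give:

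| Reading of the score | Control | CCTA-guided | Power, 100 per arm |
|---|---|---|---|
| at least 1 | 50% | 30% | 83% |
| at least 2 | 13.3% | 4.3% | 64% |
| at least 3 | 2.0% | 0.3% | 10% |
| whole score, Mann–Whitney | mean 0.65 | mean 0.35 | about 87% |

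The first three rows are exact chi-square power. The last is simulated (87.1% in 4,000 trials, 87.9% in 20,000).

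If 50% versus 30% is placed at a score of at least 2 instead, at least 1 becomes 84% versus 70% (power 66.6%), at least 3 becomes 19% versus 8% (66.5%), and Mann–Whitney has about 92%.

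**Step 3: can power for the score be stated at all?** Not from the article.

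- Keep 50% versus 30% for any component, but let patients with a positive score have the same spread in both arms (assumed 60%, 25%, 10%, 4% and 1% at scores 1 to 5). Mann–Whitney power is about 80%.
- Let only one component fall from 50% to 30%, the other five unchanged at 5% to 30% each. Mann–Whitney power runs from about 60% down to 25%. This is a different effect assumption: the any-component difference is then only 15.5 points (61.3% versus 45.8%) down to 3.4 points (91.6% versus 88.2%).
- Compare mean scores. 80% power needs a standardised difference of 2.80·√(2/100) = 0.396, which is 0.32 to 0.59 points for an assumed SD of 0.8 to 1.5.

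**Step 4: cost of leaving the choice open.** Simulate no treatment effect, and declare success if any of the four readings in step 2 reaches p < 0.05. With equal components at 10.9%, each test alone rejects in 4.1% to 5.4% of 20,000 trials, and at least one rejects in 13.8%. With unequal control rates (30, 8, 15, 15, 8 and 10%, latent correlation 0.2) the figure is 13.9%. Separate smaller runs gave 13% to 15%.

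**The case against.** The strongest reply is that one reading fits everything. Six yes/no components, an event rate near 50%, chi-square tests and odds ratios are all consistent with an event meaning at least one component present. On that reading the power is 83%, and nothing in Section 2.11 needs recalculating. This stands as far as it goes: the power claim is not disproved. But no section states that reading, and if it is intended, the declared 0–6 score is not the primary variable.

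A second reply is that an analysis plan, not shown here, may name the primary test. That is fair, and the general list of tests in Section 2.11 is not in itself a contradiction. What counts as a primary event is another matter: the article commits itself to a score in one place and to an event in another, and a later document would have to contradict one of them.

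A third reply is that Section 2.11 admits its assumptions may not hold, and that the Discussion says the CCTA-informed control group is one "which may attenuate observed differences but which enhances real-world applicability". Both remarks concern the size of rates and effects. They are disclosed, are separate from this point, and do not supply the missing definition.

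A reader might also infer that the trial is underpowered. The documents do not support that: step 3 shows that power for the score could lie above or below the stated figure. Nor do they show that type I error is uncontrolled in fact; the figure in step 4 applies only if the choice remains open until the data are seen.

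**Conclusion.** The point holds as an inconsistency in the definition of the primary endpoint. The Abstract and Section 2.9 declare a score; Section 2.11 powers a binary event without a cut-point. The calculation is correct for two proportions, but its result carries over to the declared endpoint only under a definition that the article does not give.

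The size is conditional. With equal, independent components and 50% versus 30% for any component, power runs from 10% to about 87% across the four readings. The low value at a score of at least 3 belongs to a cut that could not have the planned 50% event rate under that assumption; it shows how much depends on the cut, not what to expect. The false-positive risk of about 13–15% likewise rests on assumed component rates and on a choice made after the data are seen. It should be settled before randomization because it concerns the primary result and is cheap to repair.

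**What to change.** Before the first envelope is opened, do one of the following.

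- **(a) Binary primary endpoint.** State in Section 2.9 that the primary endpoint is a yes/no event with a named cut-point, for example at least one of the six components, and make the 0–6 score secondary. With the assumed 50% and 30% attached to that event, the calculation in Section 2.11 stands unchanged.
- **(b) Score as primary endpoint.** Keep the 0–6 score, name one test for it (for example Wilcoxon or a proportional-odds model), and replace the power sentence in Section 2.11 with the power of that test under a stated, assumed score distribution in each arm.

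Either choice is defensible; (a) is the smaller change. For (b), the feasibility phase of about 60 patients in Section 2.10 may help with the distribution, with a caution: intravascular ultrasound is encouraged in that phase and all its patients receive the CCTA report (Section 2.7), so it does not represent the control arm.

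The cost is wording and at most one recalculation. Under (b) the restated power may move in either direction.
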